## Abstract

**Background:**

Bone cement leakage (BCL) is one of the most prevalent complications of percutaneous kyphoplasty (PKP) for treating osteoporotic vertebral compression fracture (OVCF), which may result in severe secondary complications and poor outcomes. Previous studies employed several traditional machine learning (ML) models to predict BCL preoperatively, but effective and intelligent methods to bridge the distance between current models and real-life clinical applications remain lacking.

**Methods:**

We will develop a deep learning (DL)-based prediction model that directly analyzes preoperative computed tomography (CT) and magnetic resonance imaging (MRI) of patients with OVCF to accurately predict BCL occurrence and classification during PKP. This retrospective study includes a retrospective internal dataset for DL model training and validation, a prospective internal dataset, and a cross-center external dataset for model testing. We will evaluate not only model’s predictive performance, but also its reliability by calculating its consistency with reference standards and comparing it with that of clinician prediction.

**Discussion:**

The model holds an imperative clinical significance. Clinicians can formulate more targeted treatment strategies to minimize the incidence of BCL, thereby improving clinical outcomes by preoperatively identifying patients at high risk for each BCL subtype. In particular, the model holds great potential to be extended and applied in remote areas where medical resources are relatively scarce so that more patients can benefit from quality perioperative evaluation and management strategies. Moreover, the model will efficiently promote information sharing and decision-making between clinicians and patients, thereby increasing the overall quality of healthcare services.

## Introduction

1

The incidence of osteoporosis is escalating as the global population ages, causing a concomitant increase in osteoporotic vertebral compression fracture (OVCF). Annually, approximately 1.4 million new onset OVCFs are reported globally (1–3). OVCF causes low back pain, vertebral deformity, and severe functional impairment, which profoundly diminish the quality of life in the elderly population and impose substantial burdens on families and healthcare systems (4–6). Fortunately, percutaneous kyphoplasty (PKP) has become a widely adopted and effective clinical intervention for OVCF. PKP, as a minimally invasive approach, exhibits several merits, including substantial pain alleviation, partial vertebral height restoration, and early mobilization facilitation (7, 8).

However, bone cement leakage (BCL) has drawn significant attention as one of the most prevalent PKP complications, with incidence rates ranging of 5–80% (9, 10). Although a large proportion of BCLs are asymptomatic, poor outcomes still occur in specific individuals. Meanwhile, the type of complications significantly varies among different leakage locations. In particular, cement leakage into the spinal canal causes spinal cord and/or nerve root compression, potentially causing radicular pain and neurological dysfunction, which may require additional nerve decompression surgery (11). Furthermore, cement leakage into the paravertebral vein may cause serious conditions such as pulmonary embolism, cardiac perforation, cerebral embolism, and even fatality (12, 13). Additionally, cement leakage into the intervertebral disk exacerbates disk degeneration and increases the risk of adjacent vertebrae fractures (11, 14). Consequently, minimizing the incidence of BCL has become a crucial concern for surgeons. However, effective and intelligent methods to precisely predict BCL preoperatively remain lacking.

In recent years, the advent of deep learning (DL) has greatly facilitated the clinical applications of predictive models and the development of precision medicine. DL directly uses medical images as input, thereby automatically extracting effective features and leveraging computational power to integrate multimodal medical data, to construct more complex and high-performance predictive models, compared with traditional machine learning (ML) (15). However, previous studies predominantly used traditional ML techniques, mostly the traditional logistic regression models, to predict BCL (16–18). Such models somehow help clinicians in predicting BCL, but several limitations remain. First, manual imaging feature extractions are predominantly applied, which is not only time-consuming but also introduces subjectivity and selectivity, thereby potentially omitting impactful features. Secondly, no further BCL classification was conducted by current predictive models, limiting their clinical application. To the best of our knowledge, no study has developed a DL model to directly predict BCL during PKP based on preoperative medical images, which is quite difficult but valuable.

Therefore, this study aims to utilize multimodal analysis of preoperative computed tomography (CT) and magnetic resonance imaging (MRI) of patients with OVCF to develop a DL-based prediction model for accurately predicting BCL occurrence and classification during PKP. Moreover, the study will test the generalization ability of the model in prospective and multicenter datasets. The model will help spine surgeons accurately and conveniently determine patients at high risk for BCL and provide further personalized treatment options.

## Methods

2

### Study design

2.1

This study will develop a DL-based prediction system for preoperatively predicting the four subtypes of BCL during PKP based on a retrospective internal dataset, and test its performance via prospective internal dataset and cross-center external dataset (Figure 1B). Approval for the protocol has been obtained from the ethics committees of our institution. Informed consent to this study is waived as its retrospective collection of preoperative data. This study protocol was conducted following the Transparent Reporting of a multivariable prediction model for Individual Prognosis or Diagnosis (TRIPOD) statement for developing the prediction model (Supplementary Table 1) (19). Our reporting will be updated if the TRIPOD-AI statement is published during our research (20).

**Figure 1 fig1:**
[figure not shown]
Establishment and validation of deep learning prediction model for the subtypes of bone cement leakage. **(A)** The pipeline of the deep learning model. The model utilizes matched preoperative axial CT images and sagittal MRIs as input, followed by vertebra segmentation and contour recognition to generate a bounding box. The bounding box contains but is not limited to the whole vertebra volume. Next, intermediate multimodal fusion CNN-based classifiers will be used to integrate the information of the different modalities, and complete the multitask outputs. **(B)** Flowchart of the study design, including datasets, labeling, model development, and performance evaluation.

### Population

2.2

This retrospective study includes a retrospective internal dataset for DL model training and validation, a prospective internal dataset, and a cross-center external dataset for model testing. A retrospective internal dataset will be collected from consecutive inpatients of Beijing Chaoyang Hospital from January 2016 to July 2023. A prospective internal test dataset will be drawn from a prospective cohort established from August 2023 to March 2024 in Beijing Chaoyang Hospital for evaluating postoperative complications, consisting of consecutive patients undergoing PKP for treating OVCF. This prospective cohort contained intact perioperative data of participants and was registered on the Chinese Clinical Trial Registry (ChiCTR2300073507). The external dataset will be retrospectively collected from consecutive inpatients of Beijing Shunyi Hospital from January 2022 to January 2024.

### Inclusion and exclusion criteria

2.3

Inclusion and exclusion criteria are identical for both internal and external datasets. Inclusion criteria include: (1) age > 55 years; (2) diagnosis of acute or subacute OVCFs; (3) complete preoperative image data within 2 weeks preoperatively, including spine X-ray, CT, and MRI; and (4) undergoing PKP for treating OVCF. The diagnosis of acute or subacute OVCF was based on a comprehensive evaluation of history, physical examination, and radiographic evidence, which is elaborated as follows: (1) meeting the World Health Organization diagnostic criteria for osteoporosis (21), and (2) severe back pain occurred within 3 weeks, aligning with (3) tenderness or percussion pain at corresponding vertebral level, and (4) a decrease in vertebral body height or cortical disruption showed on spine X-ray, CT, or MRI, and (5) bone marrow edema shown on fat suppression T2-weighted images of MRI.

Exclusion criteria include: (1) reoperation on the index vertebral level previously undergone PVP or PKP; (2) spinal tumor, infection, or severe deformity; (3) incomplete preoperative demographic or clinical baseline data; (4) patients with neither immediate postoperative spine CT nor X-ray (within 1 week postoperatively); and (5) low image quality of spine CT or MRI.

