### Date collection

2.5

First, preoperative demographic and clinical baseline data of eligible participants, including age, sex, body mass index (BMI), bone mineral density (BMD), time from injury to surgery, fracture location, and previous OVCF, will be collected according to the medical records.

Besides, this study will collect matched preoperative spine CT images and MRIs of each patient for DL model training and validation. For both CT and MRI scan, all subjects are scanned in supine position. Image acquisition details of the internal dataset are described as follows: CT data acquisition of the spine are performed on a 64-slice MDCT scanner (Discovery CT750 HD, GE Healthcare, United States). A slice thickness of 1.25 mm and an in-plane resolution of 512 × 512 pixels were set for CT scans. Spine MRI is performed using a 3.0-T magnetic resonance system (Magnetom Verio, Siemens, GER). The scan parameters are as follows: T1WI (TR/TE, 400–600/8 ms), T2WI (TR/TE, 3,000–3,100/100 ms), T2WI-FS sequence (TR/TE, 4,000–4,200/70–80 ms), axial in-plane resolution: 256 × 224 pixels, axial slice thickness 3 mm, and intersection gap of 0.5 mm. Sagittal images were then reconstructed with an in-plane resolution of 320 × 256 pixels and a slice thickness of 4 mm. Noteworthily, most patients with OVCF usually complain of back pain at first visit, which sometimes is difficult to differentially diagnosed with degenerative spinal disease, especially in whom without definite trauma history. Hence, the reserved initial MRI may not contain continuous axial images at the fracture vertebral level in specific individuals. Therefore, we choose to collect continuous sagittal T2WI of MRI combined with continuous axial CT images, to obtain maximum information from multimodal image sources. For external dataset, spine CT is performed on a 16-slice CT scanner (SOMATOM Emotion 16, Siemens Healthcare, Germany). A slice thickness of 3.75 mm and an in-plane resolution of 512 × 512 pixels were set. MRI is performed using the same 3.0-T magnetic resonance system (Magnetom Verio, Siemens, GER) as in the internal dataset. The scan parameters were generally same except for an axial in-plane resolution of 384 × 269 pixels, an intersection gap of 0.3 mm, and a sagittal in-plane resolution of 384 × 326 pixels. All image data will be stored in DICOM files for further processing. The retrospective internal dataset will be divided into training and validation sets at a 9:1 ratio.

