### Outcomes

2.8

The primary outcome measures will be the main exactitude performance of DL model for binary predicting (0/1) different subtypes of BCL, including sensitivity, specificity, and the area under the receiver operating characteristic curve (AUROC), in both internal and external test sets. Secondary outcomes include other exactitude performance such as accuracy, precision, and F1 score. Additionally, the reliability of the model will be evaluated by calculating its consistency with reference standards and comparing it with that of clinician prediction.

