Overall, our study presents several significant advantages over previous predictive models. First, our model directly uses preoperative CT and MRI images as inputs. Previous studies have emphasized the clinical significance of radiology-related variables such as cortical destruction, intervertebral cleft, bone mineral density, fracture severity, fracture type, and basivertebral foramen sign in BCL prediction (9, 17, 29–31). In particular, Hu et al. determined only preoperative imaging parameters and intraoperative cement volume as independent risk factors for BCL after analyzing over 20 potential risk factors, including baseline characteristics, medical history-, surgery-, and radiology-related variables (17). Hence, a purely image-based DL prediction model is both adequate and reasonable. The DL model adaptively learns feature information from preoperative images without manual intervention, which enables seamless integration into current clinical workflows (32). Second, BCL is an immediate intraoperative complication without being affected by various confounding factors during long-term follow-up, improving the credibility and interpretability of our predictive model. Third, our model not only predicts the occurrence of BCL during PKP, but also enables further subtypes of leakage. Such predictive results are instrumental for clinicians in developing more thorough and personalized treatment plans. Next, our models will be trained on relatively large sample size datasets and validated with prospective, multi-center datasets, which not only improves the performance of the model, but also improves its generalization and applicability across different healthcare settings. Moreover, we will compare the prediction capability of our model with that of clinicians to test its reliability to further evaluate the performance of the model, which will provide a more comprehensive and objective evaluation of the model’s performance.

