This study has several limitations. First, the training set for the model is derived from a single-center retrospective dataset, which may introduce selection and subjective bias. Future research should use larger, prospective, and multicenter datasets to train and validate the model, thereby improving its reliability and generalizability. Second, our study solely used preoperative medical imaging data as input, omitting surgery-related variables such as surgical access, puncture pin location, and cement volume, which have been proven to be associated with BCL (9, 17, 29, 31, 33, 34). However, our model is designed to serve as a preoperative prediction tool, to conduct straightforwardly and easily personalized preoperative risk assessment and surgical planning. Finally, as the gold standard for BCL assessment remains postoperative CT examination; thus, not all patients in this study underwent postoperative CT, which may somehow result in inaccuracy of the assessment of BCL.

In conclusion, we will develop a multimodal image analysis model based on DL algorithms for predicting intraoperative BCL in PKP. To the best of our knowledge, it will be the first study to directly utilize preoperative CT and MRI images for BCL subtype prediction. Although there are numerous challenges and unresolved issues in the successful development and application of this model, its potential is highly promising. This approach facilitates individualized and intelligent preoperative assessments for patients with OVCF, providing a crucial basis for surgical decision-making. In particular, the model can be extended and applied in remote areas where medical resources are relatively scarce, so that more patients can benefit from quality perioperative evaluation and management strategies. We will continue to explore the feasibility and limitations of this model in practical clinical applications in future studies, to further improve its accuracy and utility.

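### The low-image-quality exclusion also filters both test sets, so reported performance describes patients with adequate scans and is likely optimistic for consecutive all-comers

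*Protocol article*

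**What the plan says.** Section 2.3 of the protocol article lists five exclusions, the fifth being "low image quality of spine CT or MRI". The same section opens with the statement "Inclusion and exclusion criteria are identical for both internal and external datasets".

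Section 2.2 assigns the roles. The retrospective internal data serve training and validation, and there is "a prospective internal dataset, and a cross-center external dataset for model testing". The prospective cohort is described as "consisting of consecutive patients undergoing PKP for treating OVCF", and the external patients are also consecutive inpatients. Section 2.8 measures the primary outcomes (sensitivity, specificity and AUROC for each leakage subtype) "in both internal and external test sets".

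On intended use, the Discussion says that validation in prospective, multi-center data "improves its generalization and applicability across different healthcare settings" and that "the model can be extended and applied in remote areas where medical resources are relatively scarce". Its limitations paragraph acknowledges selection bias for the training set only. It does not mention the image-quality filter on the test sets.

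**The concern.** Dropping poor scans from training is defensible. In a test set the same rule selects patients on a property of the model's own input, and one likely to be related to failure. The pipeline in section 2.7 runs in series: segmentation, bounding box, CT/MRI fusion, classification. A degraded scan can go wrong at any of these steps, and under exclusion 5 such a case never reaches the confusion matrix.

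These patients generally have a reference label. They underwent PKP, and leakage is read from separate postoperative CT or X-ray (section 2.6). Patients without such images are already removed by exclusion 4.

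Two things are at stake. A reader will take the test results as performance in consecutive patients, when they apply to a quality-selected subset. In addition, the share of patients in whom the model performs poorly or cannot run at all stays unknown, although that share matters for the settings the Discussion has in mind.

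**Working it through.** **Does the filter reach the test sets?** Three statements settle this:

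1. The criteria are identical for internal and external data (section 2.3).
2. The prospective internal and external sets are the test sets (section 2.2).
3. The primary measures are computed in those sets (section 2.8).

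Exclusion 5 therefore conditions the primary results on adequate image quality. This is a stated rule, not detail left to a fuller document.

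**How far does the external set offset this?** From section 2.5:

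- Internal CT: 64-slice scanner; "A slice thickness of 1.25 mm and an in-plane resolution of 512 × 512 pixels were set for CT scans".
- External CT: 16-slice scanner, 3.75 mm slices. The ratio is 3.75 / 1.25 = 3.0.
- External MRI: the same 3.0-T system as the internal dataset, with some differences in resolution and gap.

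The external test thus includes CT with slices three times as thick, from a second hospital. That is a real test of lower-specification CT. It is a difference in acquisition settings, though, and the scans must still pass exclusion 5. Variation in MRI equipment is hardly tested.

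**Size, by illustration.** The plan gives no figure to reproduce. It states neither the share excluded for quality nor performance on such scans, so every input here is an assumption. Let *f* be the share of low-quality scans among patients with the leakage subtype in question, *s_good* = 0.85 the sensitivity on adequate scans, and *s_poor* the sensitivity on low-quality scans.

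All-comers sensitivity = (1 − *f*) × *s_good* + *f* × *s_poor*

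Overstatement = *f* × (*s_good* − *s_poor*)

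| *f* | *s_poor* = 0.85 | *s_poor* = 0.70 | *s_poor* = 0.50 |
|---|---|---|---|
| 5% | 0.850 (0) | 0.8425 (0.0075) | 0.8325 (0.0175) |
| 10% | 0.850 (0) | 0.835 (0.015) | 0.815 (0.035) |
| 20% | 0.850 (0) | 0.820 (0.030) | 0.780 (0.070) |

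Cells show all-comers sensitivity, with the overstatement in brackets. The filtered test would report 0.85 throughout. For example, at *f* = 20% and *s_poor* = 0.50: 0.80 × 0.85 + 0.20 × 0.50 = 0.68 + 0.10 = 0.78.

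The first column is the null case: if quality does not affect performance, the filter does no harm to the estimate.

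**The case against.** A reader might infer that the test sample is simply easy to read and that the study cannot support use across settings at all. The documents do not support that. The external set comes from another hospital with a lower-specification CT and thicker slices, so some evidence across settings will exist.

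A reader might also take remote-area use to be a study aim that the design fails to meet. The aim in the Introduction is to develop the model and test it in prospective and multicenter data. Remote areas appear only as a prospect in the abstract and the Discussion, and practical feasibility is deferred to later work. No outcome is tied to low-resource sites.

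Three further objections have weight:

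- Not every excluded patient could be restored. Inclusion already requires complete preoperative CT and MRI and marrow edema visible on fat-suppressed T2 images, and a surgeon must mark the target vertebra. Some unreadable scans would fail there anyway.
- Exclusion 5 does not say that it concerns preoperative images. The pairing with MRI points that way, but if poor postoperative CT is also meant, that part protects the reference label and should stay.
- Requiring adequate input is a legitimate way to define the population a model is meant for, and a scan that cannot be processed has no score from which to compute AUROC.

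These points narrow the concern and shape the remedy. They do not remove it: otherwise eligible test patients with a poor preoperative scan and a usable postoperative image are still dropped, and the claimed use is not limited accordingly.

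**Conclusion.** The point holds in limited form. Exclusion 5 applies to both test sets, so the primary measures describe patients with adequate images and are likely optimistic for consecutive all-comers. The suggested use in resource-scarce areas remains untested for poor-quality scans.

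The upward direction rests on the assumption that the model does worse on poor scans. That is plausible, but the documents do not establish it. The size cannot be derived from the documents; the range of 0 to 7 percentage points in sensitivity shown above depends wholly on assumed values. This is an inexpensive improvement to the test design and to the wording of the claims, and it does not invalidate the study.

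**What to change.** - Restrict exclusion 5, worded for preoperative images, to the retrospective training/validation dataset.
- In the prospective and external test sets, keep every otherwise eligible consecutive patient with a usable postoperative reference image, and run the locked model on all of them.
- Report the primary measures for all processable scans alongside the adequate-quality subset. The criterion that defines the subset should be fixed beforehand and applied without knowledge of the leakage outcome.
- Report the number of low-quality and of unprocessable scans in each test set.
- Count unprocessable scans as errors only in a sensitivity analysis of sensitivity and specificity. Compute AUROC on scored scans only.
- If the exclusion is kept for the test sets, limit the claimed use in the abstract and Discussion to scans that meet the quality criterion, and list the filter among the limitations.

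The cost is a change of wording, a little more analysis on images already held, and possibly slightly lower reported performance.
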